### Data analysis

Only the data from individuals with a medication compliance rate of ≥60% will be included in primary outcome analyses. For all analyses, a *p* value of < 0.05 will be considered statistically significant and relevant corrections for multiple comparisons will be applied.

Framewise displacement—movement of the head from one volume/timepoint to the next—and scaled signal intensity differences between contiguous volumes, will be calculated for each rs-fMRI time series during the quality control process. Temporal masks will be applied to censor volumes including motion, and participant data will be excluded from analyses if more than 1/3 of the time course data requires temporal masking.

Functional connectomics involves the study of brain connectivity, first by identifying the nodes (distinct brain regions) and subsequently estimating the functional connections (network edges) between these nodes [51]. Both voxel-wise and brain atlas parcellation approaches (e.g. Gordon parcellations) [52] will be utilised to designate nodes. Data-driven, whole-brain analyses using methods such as multivariate distance matrix regression [53] and network based statistics [54] will then be applied to rs-fMRI data to characterise pharmacological effects across the functional connectome, and assess correlations with symptom measure changes. Using a similar approach to Yang et al. [55], the results of data-driven analyses will be followed up using seed-based functional connectivity analyses. Connectomic measures will be computed for BED participants at baseline and post-treatment. A paired-sample t-test will be performed to compare baseline and post-treatment connectivity profiles to confirm the treatment effect. To examine any normalisation effects of LDX in BED participants, two independent sample t-tests will be conducted to compare functional connectivity between healthy controls, and the BED group at baseline and post-treatment, respectively. To examine the association of changes in functional connectivity and clinical improvement, we will correlate change scores (Δ = BED post-treatment – BED baseline) of functional connectivity with changes in the number of binge-eating episodes.

A similar approach to that described above will be used to assess treatment-related changes in secondary outcome measures, and to examine relationships between these measures. Two group repeated-measures analyses will also be conducted to compared change scores (Δ = week 8 – week 0) between BED and control groups across tasks, to account for practise effects. For supplementary outcomes, two-sample t-tests will be performed between the pre-treatment BED and control groups.

Statistical parametric mapping (SPM12) (www.fil.ion.ucl.ac.uk/spm) and FSL (http://www.fmrib.ox.ac.uk/fsl) will be used for preprocessing neuroimaging data. Networks statistics will be computed using R package connectir (http://czarrar.github.io/connectir) and Network-Based Statistic (NBS) (https://www.nitrc.org/projects/nbs/). General statistics will be conducted using R (www.r-project.org/), SPSS (https://www.ibm.com/au-en/products/spss-statistics), and SPM.

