### Neuroimaging measures

#### Resting-state functional magnetic resonance imaging (rs-fMRI)

During the resting-state scan, participants are asked to “keep your eyes open and try to keep them on the cross. Try to remain still but not fall asleep”. A key measure extracted from this data will be connectivity strength, which is derived from the degree of synchronisation of very low frequency neuronal oscillations between each node across time. Descriptive features of the neuronal networks derived from graph-theory will also be produced, such as small-worldness, modularity and network efficiency [25].

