### Primary outcomes

Resting-state intrinsic connectivity metrics and the number of binge eating episodes, pre- and post- LDX treatment, are the primary outcome measures of this study.

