### Sample size calculation

Forty individuals with BED will be recruited for this study. At the Brain Dynamics Centre, we have a record of high treatment trial retention rates (e.g. Methylphenidate trial in child and adolescent ADHD, 98%) and minimal neuroimaging data being discarded due to excessive motion (e.g. in young adults with depression, 2–3 individuals/ 40 recruited). Based on this history, we assume there will be a final sample size of approximately 35 for the primary outcome measures. This far exceeds previous imaging studies in BED (range of 11–22 participants per study) [7, 12, 13]. In addition, the pre- post treatment design enhances power due to the use of *within subjects* rather than *between groups* comparisons. A sample size of 35 should provide approximately 80% power to observe a medium effect size of 0.5 for a two-sided statistical analysis at an alpha value of 0.05. Studies examining fMRI connectivity changes between methylphenidate (a related stimulant) and placebo have observed strong effects with sample sizes much lower than that proposed here (e.g. *n* = 12) [48–50].

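### The stated power of about 80% holds for one uncorrected paired test, but the protocol declares two primary outcomes, leaves the connectivity one open, and promises multiplicity corrections

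*Protocol article*

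**What the plan says.** The Primary outcomes section states: "Resting-state intrinsic connectivity metrics and the number of binge eating episodes, pre- and post- LDX treatment, are the primary outcome measures of this study". The connectivity metrics are plural and are not listed there.

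The measures section on rs-fMRI says "A key measure extracted from this data will be connectivity strength". It then adds graph-theory features, introduced as descriptive and by way of example: "such as small-worldness, modularity and network efficiency".

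The Data analysis section widens the choice further. On nodes: "Both voxel-wise and brain atlas parcellation approaches (e.g. Gordon parcellations) [52] will be utilised to designate nodes". On methods: "Data-driven, whole-brain analyses using methods such as multivariate distance matrix regression [53] and network based statistics [54] will then be applied to rs-fMRI data". Seed-based analyses then follow up those results. On the treatment effect: "A paired-sample t-test will be performed to compare baseline and post-treatment connectivity profiles to confirm the treatment effect". The same section sets the threshold for all analyses at 0.05 and says that multiplicity corrections will be made where relevant. It does not name the family of tests that they cover.

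The Sample size calculation section expects about 35 evaluable participants for the primary outcome measures, out of 40 recruited. It states power of about 80% for an effect of 0.5, "for a two-sided statistical analysis at an alpha value of 0.05".

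**The concern.** The power statement and the correction statement fit together only if there is one primary test. The protocol declares two primary outcomes, and the connectivity outcome can be computed in several ways, none of them marked as decisive.

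If the promised corrections span the primaries, each test runs at an alpha below the 0.05 in the power statement, and the quoted power is not delivered. If they do not span them, error across the primaries is not held at 5%. In either case a reader cannot tell in advance which connectivity result answers the main question. That choice defines the primary outcome, so it goes beyond the mechanics of a correction method, which an analysis plan could properly supply.

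**Working it through.** **Inputs.** From Sample size calculation: n = 35 evaluable pairs, 40 recruited, standardised effect d = 0.5, two-sided alpha 0.05, power about 80%. From Data analysis: a paired t-test of baseline against post-treatment. From Primary outcomes: two named primaries.

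**Step 1: reproduce the plan's figure.** Exact power of a two-sided paired t-test comes from the noncentral t distribution.
- Degrees of freedom: 35 − 1 = 34.
- Noncentrality: 0.5 × √35 = 2.958.
- Critical value at alpha 0.05: 2.032.
- Power: 82.0%. The smallest n that reaches 80% is 34.

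The stated 80% is therefore correct for one test at the full 0.05.

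**Step 2: two primaries, alpha split equally (assumed Bonferroni).**
- Alpha per test: 0.05 / 2 = 0.025; critical value 2.345.
- Power for each primary at n = 35: 72.8%.
- Pairs needed for 80%: 41, against 35 expected and 40 recruited.
- Effect detectable with 80% power at n = 35: 0.54, against 0.49 for a single test.

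**Step 3: both primaries required, each at 0.05.**
- No alpha split is needed.
- Joint power under independence, with d = 0.5 for both: 0.8195² = 0.672, about 67%.
- Joint power can be no higher than the weaker of the two tests. It would approach 82% if the binge-episode effect were much larger than 0.5, or if the two test results were very strongly correlated in the hypothesised direction.

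**Step 4: neither rule, each primary tested at 0.05.**
- Chance of at least one false positive under independence: 1 − 0.95² = 0.0975, or 9.8%.
- This is an upper bound; correlation between the two tests lowers it.

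**Step 5: more connectivity tests (illustration only).** With an equal Bonferroni split over 4 tests, alpha per test is 0.0125, power is 62.7%, and 48 pairs are needed for 80%. The plan does not fix the number of tests, so this shows the direction of the effect and is not an estimate for this trial.

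**The case against.** The strongest reply is that the protocol does promise corrections and that an analysis plan, not shown, may define their family and method. That is fair: the missing correction method is not the finding. But any correction that reaches across the primaries makes the per-test alpha smaller than the one used for power, and both statements are in this document.

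A second reply is that the study is mechanistic. The Background admits that precise connectivity hypotheses are hard to form, and the Discussion says the study is not designed to assess efficacy. An exploratory label would be a legitimate answer, but the protocol instead declares primary outcomes, a significance threshold and a power figure.

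A third reply is that, with alpha split, the chance that at least one primary succeeds is higher than 72.8%: 1 − (1 − 0.728)² = 0.926 under independence. This is correct. However, success on binge episodes alone would not answer the primary aim, which concerns neural mechanism.

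A reader might go further and infer that a positive result on any connectivity route counts as success, with a false-positive rate far above 5% across many routes. The documents do not support this. No section gives such a rule. Seed analyses are sequential follow-ups and graph features are described as descriptive. Nothing says that every node scheme is crossed with every method. The routes also re-analyse the same scans, so treating them as independent would overstate the error, and Bonferroni would understate power.

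**Conclusion.** The point holds in a limited form. The quoted power is right for one uncorrected paired test, but the protocol offers it for primary outcome measures that comprise at least two tests, one of them undefined.

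With the two named primaries alone, the shortfall from the reproduced 82.0% is about 9 percentage points per outcome under an equal split (72.8%), or about 15 points if both must succeed and are independent (67%). Without either rule, error across the two is at most 9.8%.

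These figures assume d = 0.5 for both primaries and 35 evaluable pairs. They also assume that the connectivity effect can be expressed as a paired mean difference, which is only approximate for distance matrix regression or network-based statistics. The two-primary result does not depend on counting connectivity routes.

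**What to change.** Before results are seen:

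1. Name one primary connectivity test. One whole-connectome pre/post test on one stated parcellation, family-wise corrected at 0.05, would serve; the choice is the sponsor's.
2. Label the other node schemes, methods, graph metrics and seed follow-ups secondary or exploratory.
3. State whether both primaries are required, alpha is split between them, or one is demoted.
4. Restate power for that choice at the planned enrolment. If one test is the sole primary, the 0.05 and 80% can stand for it, provided that its effect can be expressed as a paired d of 0.5.

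This changes wording only: enrolment is unchanged and every planned analysis still runs. The cost is that fewer results can be called primary and that the stated power may fall. Under an equal split, 80% is out of reach at 40 recruited, so the protocol would have to quote the lower power.

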It is widely recognised that cognition and behaviour arise from the dynamic interactions of distributed brain areas operating in networks. These large-scale networks can be imaged during functional tasks that evoke their activity, or during rest, when they tend to produce highly synchronised, very low frequency neuronal oscillations [25]. Analysis of resting-state functional magnetic imaging (rs-fMRI) can reveal much about the innate organisation of the brain, by demonstrating how brain regions, or nodes, are organised within networks, and how various networks are intrinsically connected with one another [26]. Applying a connectomic approach increases potential for providing new insights into the neural mechanisms of pharmacotherapy by providing comprehensive descriptions of these intrinsic connectivity patterns [27, 28].

There are currently no studies published on intrinsic connectivity patterns in BED relative to controls. As such, it is difficult to hypothesise precisely how LDX will effect neural connectivity in this group. Given the known dysfunction in the fronto-striatal regions relating to reward and inhibition in BED, it is assumed however that effective treatment with LDX will “normalise” activity and connectivity within these networks. We will also be able to examine relationships between treatment-driven neural changes and a large range of symptom measures and objective laboratory-based measures of cognition. These secondary meaures may also help to determine whether LDX exerts beneficial effects more broadly to non-food inhibitory control and other general cognitive improvements.

The primary aim of this study is to provide a comprehensive understanding of the neural mechanisms by which LDX improves symptoms of BED. We hypothesise that LDX will act by normalising connectivity within and between brain circuits responsible for reward and impulse control. Further, we hypothesise that a reduction in binge eating behaviours will correlate with normalised activity and connectivity of brain regions within reward and impulse control networks. Secondary aims include examining treatment-related changes in cognitive performance and other self-reported measures of symptoms and behaviour.

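### A paired t-test on connections chosen from the same scans cannot confirm the treatment effect; the corrected whole-brain test should carry the inference

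*Protocol article*

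**What the plan says.** All references are to the Protocol article.

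- **Primary outcomes** names resting-state intrinsic connectivity, before and after treatment, as a primary outcome alongside binge eating episodes.
- **Background** gives the hypothesis: "We hypothesise that LDX will act by normalising connectivity within and between brain circuits responsible for reward and impulse control".
- **Data analysis** sets out a sequence. Whole-brain methods (multivariate distance matrix regression, MDMR, and network-based statistics, NBS) look for drug effects and for correlations with symptom change. Next, "the results of data-driven analyses will be followed up using seed-based functional connectivity analyses". Connectomic measures are computed at both time points. Then: "A paired-sample t-test will be performed to compare baseline and post-treatment connectivity profiles to confirm the treatment effect". Comparisons with controls at each time point follow, and finally a correlation of connectivity change with change in binge eating episodes.
- On multiplicity, the same section says for all analyses that "relevant corrections for multiple comparisons will be applied".
- **Sample size calculation**: "Forty individuals with BED will be recruited for this study", and "we assume there will be a final sample size of approximately 35 for the primary outcome measures". No split sample, cross-validation or replication cohort is described.

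**The concern.** A test confirms a finding only if it could have failed independently of the step that produced the finding. Here one group of patients with one pair of scans supplies both the search and, on the natural reading, the follow-up test. A connection picked because it changed from baseline to week 8 will tend to show a change from baseline to week 8 when those scans are tested again. The promised multiplicity correction controls error within a family of tests. It does not make a second look at selected data independent, and it does not remove the upward bias in the selected effects.

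At stake is what the trial may claim on a primary outcome. A reader would take a confirmed effect as a second piece of evidence when it is the first one restated. The same applies to the control comparisons if they use the selected connections, because noise that enlarges the pre-post change also pushes the baseline and post-treatment values apart. It applies likewise to the change-score correlation, since the whole-brain stage has already searched for correlations with symptom change.

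**Working it through.** **Inputs from the article (Sample size calculation).** n = 35 analysable; paired pre-post comparison; tests two-sided at the 5% level. The stated power is: "A sample size of 35 should provide approximately 80% power to observe a medium effect size of 0.5".

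**Assumptions, not in the article.** Selection thresholds of 0.05 and 0.001; 10 to 333 candidate seeds, independent of each other; 20 edges per node in the multivariate case.

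**1. The plan's own figure.** Paired t-test, df = 34, noncentrality 0.5 × √35 = 2.96. Exact power from the noncentral t distribution is 82.0%, which agrees with the stated figure of about 80%. So the paired contrast at n = 35 is the right model for the next steps.

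**2. Selection and re-test by the same test.** Something selected at p<0.05 has by definition p<0.05 when the same paired test is repeated on the same data. The re-test passes with probability 1 and adds nothing.

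**3. Size of the bias.** The smallest |d| that can pass is t_crit/√n: 2.032/5.916 = 0.34 at p<0.05, and 0.61 at p<0.001. Any selected result must exceed this, whatever the truth. Mean observed d among selected results (simulated):

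| True d | Selected at p<0.05 | Selected at p<0.001 |
|---|---|---|
| 0.2 | 0.45 | 0.69 |
| 0.3 | 0.48 | 0.70 |
| 0.5 | 0.57 | 0.74 |

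For a true d of 0.3 the inflation is 0.476/0.3 = 1.6-fold and 0.698/0.3 = 2.3-fold.

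**4. Top seed re-tested with no selection threshold, null case.** The chance that the largest of R independent seeds shows p<0.05 is 1 − 0.95^R.

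| R | Formula | Simulated, same data | Simulated, independent data |
|---|---|---|---|
| 10 | 40% | 42% | 4.4% |
| 50 | 92% | 92% | 5.3% |
| 100 | 99.4% | 99.5% | 5.3% |
| 333 | 100% | 100% | 4.5% |

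With R = 100 the top null seed averages |d| = 0.50, the effect size the trial is planned around. Correlated seeds would lower the same-data rates here but would not alter step 2.

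**5. Selection by a node-level multivariate statistic, null case.** In a crude MDMR-like simulation, the node with the largest sum of squared t over 20 edges is selected and its edges are tested on the same data. Single edges pass at 16% (100 nodes) to 18% (333 nodes) instead of 5%, and at least one edge passed in every run. The re-test is inflated but not automatic.

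**6. Validity of the first stage.** If the whole-brain stage is family-wise corrected (Bonferroni simulated), a false seed is selected in about 4–5% of null data sets. The whole-brain inference stands; only the follow-up lacks independent meaning.

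**The case against.** The strongest defence is that the article does not say outright that the paired t-test uses the selected seeds. The seed follow-up is one sentence, the computation of connectomic measures another, and the t-test then refers only to connectivity profiles. These could be connectomic measures in general, such as the graph metrics listed under Neuroimaging measures. Details may also lie in the cited study whose approach is followed, or in the full protocol. This stands, and it makes the finding conditional. Describing a corrected omnibus result with seed maps is also legitimate.

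Three stronger readings are tempting and are not supported:

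- *Whatever is selected is always confirmed.* That is exact only when both stages use the same contrast and statistic (steps 2 and 5).
- *Many null connections would pass and be declared confirmed.* That supposes uncorrected edge-by-edge selection. The article names multivariate and network-level methods and promises correction.
- *The reward and impulse-control hypothesis gets no valid test.* The corrected whole-brain test covers those circuits. The Background explains that, with no published intrinsic-connectivity studies in this disorder, precise prediction is difficult. Fixed seeds as the primary test are a design preference, and a condensed article may leave a seed list to the full protocol.

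None of this rescues the word *confirm* if the test is run on connections selected from the same scans.

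**Conclusion.** The point holds in conditional form. If the paired t-test is applied to connections or seeds selected for the same pre-post change in the same participants, it cannot confirm the treatment effect. Its p-value depends on the selection and its effect size is too large. The null pass rate of the re-test ranges from about 16–18% per edge with a multivariate selector to certainty with the same test at p<0.05 or stricter, against a nominal 5%. These sizes rest on the assumed thresholds, seed counts, edge count and independence; the direction of the bias does not. The corrected whole-brain inference is unaffected. If the t-test is meant for measures not chosen from these data, the circularity disappears, but the article must say so.

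**What to change.** In Data analysis:

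1. State that the family-wise-corrected whole-brain test is the inferential result for the treatment effect on connectivity.
2. Drop the claim that the paired t-test confirms the effect. Label seed maps and paired t-tests on selected connections as post hoc and descriptive, with no confirmatory p-value or effect-size claim.
3. Give the same label to the control comparisons and the change-score correlations wherever they use the selected connections.
4. If the paired t-test is meant for measures not selected from these data, name them.
5. Optionally, if a confirmatory test on the hypothesised circuits is wanted, fix a short set of reward and impulse-control networks before any post-treatment scan is analysed, with correction across that set.

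Items 1 to 4 cost only wording and need no new data or scans. Item 5 needs a decision before post-treatment data are examined. The downside is that fewer results can be called confirmed.

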### Overall study design

This study is a repeated-measures pre-post treatment design. Repeated-measures data from a control group is being collected at week 0 and week 8 for normative comparisons. Figure 1 outlines the timeline of events.

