#### Post-treatment session (week 8)

BED participants return the self-monitoring sheets provided during the baseline session and any unused tablets at the follow-up session. The majority of the assessments undertaken at session 1 are repeated at session 2 for both BED and control participants. The assessments/tasks that are not performed in session 2 are the SCID-5-RV and MINI, structural MRI and diffusion weighted imaging (DWI), and the Wechsler Test of Adult Reading [32] (WTAR). This session takes approximately 5 h to complete.

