## Discussion

The combination of neuroimaging and laboratory-based cognitive measures will provide a sophisticated and comprehensive explanation of the neural mechanisms by which LDX improves BED symptomology. The repeated measures design will enable participants to act as their own controls in assessing whether LDX changes interconnectivity and integration, particularly in brain regions responsible for reward sensitivity and impulse control. We can also assess whether interconnectivity and integration post-treatment more closely resembles healthy controls, relative to pre-treatment.

A limitation of this study is that we are unable to draw absolute conclusions on the causality of LDX in our results as the design does not include a placebo arm. There are confounding factors that could contribute to changes in neural connectivity and binge eating symptomology, for instance, use of a self-monitoring diary, clinician-patient interaction during study assessments and other social and environmental factors. While we may not be able to attribute changes in BED symptomology and neural connectivity solely to the effects of LDX, the results are more generalisable to a real-world setting where these factors exist and contribute to treatment effects. As this study is not designed to assess treatment efficacy, accounting for placebo effect is not required. Another limitation is that the primary measure of binge-eating behaviour, the number of binge eating events, is based on self-report, which relies on memory and unbiased reporting for accuracy. Finally, more information is required on the longer term efficacy and safety implications of LDX treatment, however this is beyond the scope of the current study and should be a direction for future research.

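### The primary resting-state change is tested in BED participants alone, so a rescan shift shared with the controls cannot be separated from the LDX effect

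*Protocol article*

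**What the plan says.** The Primary outcomes section states: "Resting-state intrinsic connectivity metrics and the number of binge eating episodes, pre- and post- LDX treatment, are the primary outcome measures of this study". For the imaging outcome, Data analysis says "Connectomic measures will be computed for BED participants at baseline and post-treatment", and then "A paired-sample t-test will be performed to compare baseline and post-treatment connectivity profiles to confirm the treatment effect".

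Controls enter the connectivity analysis through two independent-sample t-tests, one against BED at baseline and one against BED after treatment. The article does not say which control session is used in either.

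Controls are measured twice. Overall study design says "Repeated-measures data from a control group is being collected at week 0 and week 8 for normative comparisons", and the week 8 section says "The majority of the assessments undertaken at session 1 are repeated at session 2 for both BED and control participants". That section lists what is left out at the second session: the two diagnostic interviews, structural MRI, diffusion imaging and the adult reading test. Resting-state fMRI is not on the list, so control rescans should be available.

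The article does plan a two-group comparison of week 0 to week 8 change. It stands in the paragraph on secondary outcomes and is made "between BED and control groups across tasks, to account for practise effects".

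**The concern.** The article accepts, for the tasks, that measuring people twice can move scores without any drug, and that the change in untreated controls is the way to allow for it. It does not carry this reasoning over to the primary imaging outcome. Familiarity with the scanner at a second visit, or drift in the scanner itself, could shift connectivity in both groups. In a BED-only paired test, any such shift adds to the drug effect and cannot be told apart from it. With no placebo arm, the control rescans are the only data in the study that can estimate a shared shift, and they would already have been collected.

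The normalisation tests do not fill the gap. One significant and one non-significant cross-sectional result does not show that the groups changed differently. With the control session unnamed, the second test could itself carry the shift.

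**Working it through.** **Inputs.** From Sample size calculation: about 35 analysable BED participants, effect size 0.5, two-sided alpha 0.05, power about 80%. From Participants: 22 controls. Assumed, because the article gives no figure: the size of the session shift, and equal SDs of the change score in the two groups. All effects below are in SDs of the change score.

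**1. The plan's own figure.** A paired t-test with n = 35 has 34 degrees of freedom and noncentrality 0.5 × √35 = 2.958. The noncentral t distribution gives power 82.0% (normal approximation 84.1%; n = 34 already gives 80.8%). The stated figure of about 80% is reproduced. It is the power of the paired test only.

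**2. What each analysis estimates.** Let δ be the change in BED beyond any shared shift, s the shift common to both groups, and g the BED-minus-control difference at week 0.

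- Paired test in BED: δ + s.
- BED change minus control change: (δ + s) − s = δ.
- BED baseline v controls at week 0: g.
- BED post-treatment v controls at week 0: g + δ + s.
- BED post-treatment v controls at week 8: (g + δ + s) − s = g + δ.

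If week 0 controls serve in both normalisation tests, s enters only the second and can mimic or mask normalisation. If sessions are matched, s cancels within each test. Even then, the quantity of interest is the difference between the two contrasts, (g + δ) − g = δ, and two separate tests do not test that difference.

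**3. Rejection rate of the paired test with δ = 0.** The noncentrality is s × √35.

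| Assumed s | Noncentrality | Paired test rejects |
|---|---|---|
| 0 | 0 | 5.0% |
| 0.1 | 0.592 | 8.9% |
| 0.2 | 1.183 | 21.0% |
| 0.3 | 1.775 | 40.7% |

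A simulation with 40,000 runs agrees. At s = 0.2 the paired test rejected in 21.1% of runs and the two-group change test in 5.0%. At s = 0.3 the figures were 40.9% and 4.9%.

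**4. Cost of the two-group contrast.** The standard error of the mean BED change is 1/√35 = 0.169. That of the difference in change is √(1/35 + 1/22) = √0.0740 = 0.272. At d = 0.5 the noncentrality is 0.5/0.272 = 1.838 on 35 + 22 − 2 = 55 degrees of freedom, so power is 43.9%, against 82.0% for the paired test. The difference detectable with 80% power is about 0.78 SD. If only 19 or 20 controls had usable scans, power would be 40.6% or 41.8%, and the detectable difference about 0.815 or 0.80 SD.

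**The case against.** Several points can fairly be made for the plan.

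- **Attribution is already limited.** The Discussion says that without a placebo arm the changes cannot be put down to LDX alone, and its list of other influences is given as examples. This stands, and it makes the fault milder. But the examples do not include rescan effects, the concession does not explain why the control rescans go unused here, and it sits badly with a test said to confirm the treatment effect.
- **The paired test is not the whole analysis.** Whole-brain methods come before it, and corrections for multiple comparisons are promised. This stands: the rejection rates above describe one uncorrected test with an assumed shift and are illustrations only.
- **An article condenses its protocol.** This would answer a complaint about missing detail. Here the article itself states which test serves the primary change and where control change is used.
- **The contrast is imprecise, and the within-subject design was chosen for power.** This stands, and it rules out making the contrast a condition for any conclusion.

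A reader might also infer more than the documents support.

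- **Head motion passing as a drug effect.** Data analysis computes framewise displacement, censors affected volumes, and excludes participants with more than one third of the time course masked. Only residual motion is left. The article does not say that LDX changes movement in the scanner, and covariate detail is commonly left to a fuller document.
- **The placebo sentence contradicting the aim.** The Discussion says: "As this study is not designed to assess treatment efficacy, accounting for placebo effect is not required". The argument may be weak, but efficacy is taken from earlier placebo-controlled trials and the aim is mechanistic. It is in any case a separate matter, which untreated healthy controls cannot address.
- **Attributing change to LDX wherever BED change exceeds control change.** Such a rule would not be justified, because placebo response, regression to the mean and BED-specific change would all remain in the contrast.

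**Conclusion.** The point holds in a limited form. For the primary resting-state outcome, the article tests change in BED alone and does not use the control change that it uses for tasks, although the same participants are rescanned. A shift shared by both groups is therefore inseparable from the LDX effect in that test, and the normalisation tests do not separate it.

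The size of the problem is unknown because the article gives no session shift. Over an assumed range of 0.1 to 0.3 SD of the change score, a single paired test at n = 35 would reject in about 9% to 41% of trials with no drug effect. With no shift, the test keeps its 5% level. The point concerns the imaging outcome only, not binge eating episodes. It is a worthwhile improvement and does not invalidate the design.

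**What to change.** 1. Keep the paired test as the estimate of within-BED change, and confine the 80% power statement to it.
2. Extend the planned BED-versus-control comparison of change scores to resting-state connectivity. Report it as a supportive estimate with its confidence interval, not as a gate.
3. State which control session enters each normalisation test, matched by session: week 0 controls with BED baseline, week 8 controls with BED post-treatment.
4. Describe the paired result as change during LDX treatment, in line with the limitation in the Discussion.
5. State that the control contrast removes shared session effects only.

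A sensitivity analysis with mean framewise displacement is optional. Displacement may itself be affected by treatment, so adjusting for it is not neutral.

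The cost is some extra analysis and a few sentences, with no new data. The main drawback is the imprecision of the contrast: about 44% power at d = 0.5 with 35 v 22, so a non-significant result would not show that there was no effect.
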